# Efficacy, safety and cost-effectiveness of a web-based platform delivering the results of a biomarker-based predictive model of biotherapy response for rheumatoid arthritis patients: a protocol for a randomized multicenter single-blind active controlled clinical trial (PREDIRA)

**DOI:** 10.1186/s13063-020-04683-7

**Published:** 2020-08-31

**Keywords:** Rheumatoid arthritis, Personalized medicine, Prediction models, Anti-TNFα agents

## Abstract

**Background:**

Rheumatoid arthritis (RA) is one of the leading chronic inflammatory rheumatism. First-line therapy with synthetic disease-modifying antirheumatic drugs (sDMARD) is insufficiently effective in 40% of cases and these patients are treated with biotherapies. The increased use of these drugs each year is becoming a public health issue with considerable economic burden. This cost is 20 times higher than that of sDMARD. However, among patients treated with biotherapies, clinical practice shows that about one third will not respond to the selected drug. In nonresponse cases, practitioners currently have no choice but to perform an empirical switching between different treatments, because no tool capable of predicting the response or nonresponse to these molecules is currently available.

**Methods:**

The study is a prospective, phase III, controlled, multicenter, and randomized, single-blind (patient) clinical trial, including RA patients with a previous failure to anti-TNF therapies. The main objective is the analysis of the clinical and pharmacoeconomic impact after 6 months of treatment. Intervention arm: prescription of biotherapy (rituximab, adalimumab, abatacept) using SinnoTest® software, a prediction software based on proteomic biomarkers. Control arm: prescription of biotherapy based on current practice, without the SinnoTest® software (any biotherapy). In addition, a substudy will be carried out within this trial to generate a biobank and further analyze the proteomic profile of the patients and their modification throughout the study.

**Discussion:**

This clinical trial study will be the first validation study of a biotherapy response prediction software, bringing personalized medicine into the management of RA. We expect that the findings from this study will bring several benefits for the patient and the Health Care System.

**Trial registration:**

ClincalTrials.gov NCT04147026. Registered on 31 October, 2019.

## Introduction

### Background and rationale {6a}

Rheumatoid arthritis (RA) accounts for a large proportion of chronic inflammatory rheumatisms (CIR), with a prevalence of 0.4% in the Caucasian population [1] and an incidence of 9/100,000 subjects [2]. Chronic inflammation is clinically manifested by pain and morning stiffness and can lead to joint destruction, often leading to major functional disability in the medium term [3]. RA is the result of the interaction between genetic and environmental factors leading to increased circulating levels of many cytokines. The inhibition of these cytokines, such as tumor necrosis factor (TNFα) or interleukin (IL)-6, is a logical approach, which has introduced profound changes in the management of this condition.

Gradually since the 2000s, biological disease-modifying antirheumatic drugs (bDMARDs) were added to the existing therapeutic arsenal. There are currently available several bDMARDs, including TNFα antagonists, anti-IL-6 receptor, anti-IL-1, a T cell anti-activator, and a CD20+ anti-B lymphocyte [4]. In addition, new bDMARDs are expected to be approved for treatment of RA in the following years, making the therapeutic management of these patients even more complex.

One of the major current challenges in RA management is being able to predict drug responsiveness before treatment initiation [5], as there are no tools able to predict the response to a particular medication [6]. Rheumatologists lack evidence-based knowledge to choose the most suitable DMARD for their patients, and these drugs are prescribed in a “trial-and-error” manner. In case of a lack of response (which has been reported around 30–50% for bDMARDs [3, 7]), the physicians have to perform an empirical rotation between the different drugs, until the correct drug, or combination of drugs for this particular patient is found. Therefore, nonresponders are unnecessarily exposed to undesired adverse events along with the worsening of their physical condition. Furthermore, the ineffective use of bDMARDs has a dramatic economic burden due to their important costs [4]. A study by Meissner and colleagues [8] shows a greater overall economic impact on the health system of patients who changed bDMARD following failure of a first biological compared to those who did not change. This economic burden is even greater when the patient has to change his/her treatment for a second time. This phenomenon seems difficult to reverse in case of initial misdirection, since the probability of a patient who has already received an anti-TNF to respond to another biological treatment decreases gradually according to the increasing number of failures of previous treatments [9]. A tool able to provide a probability score of response or nonresponse to specific treatments could pose an important benefit for clinicians and patients.

In order to improve the response rate to bDMARDs, research for predictive biomarkers of therapeutic response has been active for more than 15 years [10]. Several approaches have been followed to identify biomarkers, including genomics, transcriptomics, epigenetics, and proteomics. However, not all of these strategies have contributed benefits at present. Indeed, in the genomics field [11], the search for candidate genes and the replication of results on different cohorts is fragile and tedious. The hypothesis of several associated genes each having a low impact is preferred over that where few genes each with a significant effect would be involved. Its routine use remains complex. Similarly, epigenetics has provided very preliminary data for the time being [12, 13]. Finally, the study of the transcriptome makes it possible to identify a certain number of genes, but its widespread use by clinicians as part of their regular assessment of their RA patients is difficult on a daily basis [14], and the study of the serum metabolome remains complicated [15].

The proteomic approach, on the other hand, is innovative and simpler to use in routine: it is focused on proteins, which are the terminal elements of cellular actions. It has been emerging in research for about 10 years in rheumatology for the theranostic side [16, 17], but clinical applications are not routine. The latest developments in this area, especially those carried out by members of the PREDIRA consortium, could change the management of these patients [16, 18, 19]. These studies have made it possible to characterize biomarkers differentially expressed at baseline in patients who respond to a bDMARD compared to weak or nonresponders, hoping to optimize a targeted prescription of bDMARDs [16, 17, 20]. In order to allow a rapid translation to clinical practice, our approach prioritizes the selection of biomarkers for which validated diagnostic assays exist, are routinely used, and are commercially available. Several predictive algorithms aimed at 3 classes of bDMARDs have been developed: Anti-TNFa (adalimumab), inhibitors of costimulation of T cells (abatacept), and anti-B-cell antigen CD20:(rituximab).

Based on identified biomarkers and predictive algorithms [16, 18, 19], an application called SinnoTest® has recently been validated [21–23] to determine a priori the most appropriate treatment for the patient with RA according to its clinical context (patients with a previous failure to bDMARDs), depending on its specific proteomic profile (predictive and personalized medicine). This medical device has also been CE marked/approved since August 2018. In practice, from a simple biological sample of a patient, such as blood (plasma or serum), specific protein biomarkers are quantified using routine techniques, allowing after combination through an algorithm, to associate the patient’s profile at a personalized response or nonresponse status for these biotherapy rotational patients. An online interface allows the rheumatologist to access, for each patient, the results of biomarker analysis, as well as the probability of response to different biotherapies available on the market.

We hypothesize that the SinnoTest® software offers real-world clinical and pharmacoeconomic benefits by integrating the main biotherapies currently available. This study will target patients with RA in rotation of a first biotherapy due to inefficiency or toxicity. The expected economic impact is multiple: change in the use of care (hospitalizations, medicines, regular biological controls, outpatient stays, consultations, nursing, surgery, transportation, etc.); reduction of the costs related to the losses of production (reduction of the incapacities at work inducing absenteeism, long-term work stoppages, permanent disability ...); reduction of intangible costs, the assessment of which is difficult but which represents an expected social benefit of such a care strategy. In addition, we will try to show that SinnoTest® also has a strong clinical impact in terms of early-adapted management via the responder rate.

### Objectives {7}

The primary objectives of this clinical trial is to study the clinical and pharmacoeconomic impact after 6 months of the use of the SinnoTest® predictive tool in patients with rheumatoid arthritis who have failed to a first anti-TNF biologic agent compared to usual care. The secondary objectives will be:
Pharmacoeconomic: to carry out a budget impact analysis (BIA) at 6 and 12 months;Clinical: to describe the performance of the software’s predictive model on new clinical data from the 6-month trial.

We will also carry out a proteomics substudy with the objectives of comparing the variation of the proteomic profile between the M0 (date of inclusion) and the M6 (end of study date). The achievement of this objective will be based on the constitution of a biobank, which will serve as a basis for future studies focused on the therapeutic management of these patients.

### Trial design {8}

This project is a prospective phase III randomized clinical trial in 2 parallel groups, multicenter, controlled (prescription of bDMARD with or without the SinnoTest® software), and single-blind (the patient will not know if his bDMARD treatment has been prescribed with or without the help of SinnoTest® software). The inclusion period will be 12 months. Each patient will be followed up to 6 months (clinical evaluation) and up to 12 months (for the analysis of the budgetary impact at 12 months) post randomization.

## Methods: participants, interventions and outcomes

### Study setting {9}

The population studied concerns patients with rheumatoid arthritis, who have failed a first anti-TNF medication (due to inefficiency or adverse events), and attend rheumatology outpatient clinics from tertiary care centers in the Madrid Region (Spain). This situation corresponds to a very large majority of patients admitted to rheumatology consultations.

### Who will take informed consent? {26a}

Informed consent will be obtained by a practicing rheumatologist, able to prescribe any of the drugs that the study subject may receive, and a member of the study team.

The Investigator will be responsible for providing each patient with an information sheet about the trial and the objectives, methods, foreseeable benefits, and potential risks of the study, which should be read by the patient. The investigator must explain to the patients that they are totally free to refuse their participation in the study or to abandon it at any time and for any reason. The Investigator will be responsible for obtaining the written informed consent of each of the participating patients before proceeding with any medical procedure of the study. The investigator will be responsible for not involving any patient in the study without having previously obtained their voluntary consent in writing.

### Additional consent provisions for collection and use of participant data and biological specimens {26b}

In addition, for the proteomics substudy, a second independent informed consent will be collected, which will also include the possibility of storing the samples not used in the present study in the biobank of the center where it is carried out in the study and in the Biobank of the Center Hospitalier Universitaire Grenoble Alpes (France).

### Interventions

#### Explanation for the choice of comparators {6b}

##### Intervention description {11a}

The patients will be randomized to an intervention group (SinnoTest®) or an active-control group (usual care). Patients allocated to the intervention arm will receive the prescription of bDMARD (rituximab, adalimumab, abatacept) using SinnoTest® software, while those allocated to the control arm will receive the prescription of bDMARD without the SinnoTest® software which corresponds to current practice (all bDMARDs).

##### Innovative procedure

*Innovative Medical Device (IMD): SinnoTest® Software version 2.0*

SinnoTest® is a therapeutic guidance device for patients suffering from chronic inflammatory rheumatism, in particular RA. SinnoTest® consists of the following three elements: “routine” biological assay of biomarkers from a blood sample, calculation algorithm, and graphical user interface (software and online application). This device was designed by the company Sinnovial. The assessment of its conformity was carried out by SurgiQual Institute.

Biomarkers are detected and quantified in blood samples of patients, using commercial tests aimed at determining the levels of these molecules. These results are sent to the SinnoTest® secure server. These data are processed by algorithms to determine the probability of response to the treatments available in the therapeutic arsenal (biological therapies). These algorithms were developed in a population of patients with a previous failure to iTNFs receiving the specific medication the algorithm was designed for. This data is sent to a secure server. The graphical user interface is an independent software, accessible through a web platform, which allows authorized health professionals to access the results of the analysis of individual patients. SinnoTest® is a stand-alone IMD-MD software, accessible via a web platform. Rheumatologists from the different centers will be contacted by email to register for the SinnoTest® online platform. A link in this email will provide access to the registration part of the application. The rheumatologists will then be able to connect to the SinnoTest® platform thanks to their personal identifiers.

*Process of the innovative procedure*

The selection of the bio-drug is carried out based on the recommendations of SinnoTest®. This test categorizes bDMARD based on the probability of response. It will allow to prescribe both original molecules and biosimilars in an equivalent way. In the SinnoTest® arm, the investigator prescribes the treatment defined as the most effective by SinnoTest®, except in case of contraindication. If contraindicated, the investigator prescribes the second-choice treatment (if any) of SinnoTest® in terms of efficacy.

The bDMARDs possibly recommended by SinnoTest® are adalimumab, rituximab, and abatacept. Not being exhaustive in terms of biotherapies, it is possible that the SinnoTest® cannot recommend any bDMARD. In this case, the rheumatologist may prescribe one of the following other bDMARDs: etanercept, adalimumab, infliximab, certolizumab, tocilizumab, sarilumab, abatacept, anakinra, golimumab, or rituximab.

##### Reference procedure

There is currently no evidence of treatment response in RA. The choice of the treatment by the rheumatologist is therefore empirical. In order to simplify the process and favoring blinding, regardless of which arm the patient is randomized to, the usual rheumatologist will record two treatment proposals in the clinical history. On the one hand is the treatment that he would prescribe if the patient was randomized to the control arm and, on the other hand, the one that he would prescribe if the patient was randomized to the intervention arm and if SinnoTest® did not recommend any treatment (therefore, the proposed treatment in this case cannot be any of the 3 potentially recommended by SinnoTest®).

At the successive visit after 6–10 days in which the bDMARD will be prescribed, if the patient was randomized to the control arm, or was randomized into an intervention group, but SinnoTest® did not recommend any bDMARD, the medication previously registered by the usual rheumatologist will be used.

*Process of the reference procedure*

This is the current management of patients with RA, based on the EULAR recommendations. In case of rotation of biotherapy after prescription of a first biotherapy, the rheumatologist may prescribe the following bDMARDs: etanercept, adalimumab, infliximab, certolizumab, tocilizumab, abatacept, anakinra, golimumab, rituximab. All these bDMARDS can be prescribed as well as their biosimilars. In case of remission of more than 6 months, a reduction (dosage or spacing of the catch) of the biotherapy can be considered.

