### Assignment of interventions: blinding

#### Who will be blinded {17a}

Study subjects will be blinded to the intervention (who decides the medication prescribed). Evaluators will also be blinded to the intervention where the subject was allocated.

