### Adverse event reporting and harms {22}

In each study visit, the presence of the most common adverse events related to the study medication will be actively inquired by the blind investigator, including
-Infections including pulmonary and urinary infections and opportunistic infections including tuberculosis;Nausea, vomiting, abdominal pain, diarrhea, tiredness, dizziness, and headache;Liver problems;Hematological disorders: agranulocytosis, thrombocytopenia, anemia, aplasia;Demyelinating diseases: multiple sclerosis and optic neuropathies;Heart failure;Stevens-Johnson syndromes and Lyell syndromes;Psoriasis;Interstitial pneumonitis;Hypersensitivity reactions: fever, chills, pruritus, urticarial, dyspnea, chest pain, hypotension or arterial hypertension, and reactions to injection sites

Regarding the notification of severe adverse events, we will follow the definitions and guidelines of the document MEDDEV 2.7/3 review 05/03/2015 “Guidelines on medical devices: Clinical investigations: Serious adverse event reporting under Directives 90/385/EEC and 93/42/EEC”.

All adverse events will be followed until its resolution, subject’s death, or lost to follow-up.

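### Control-arm drug proposals kept in the clinical history could unblind an evaluator who reads them and knows the drug given

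*Protocol article*

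**What the plan says.** Reference procedure sets the recording step and where it is kept. In both arms, "the usual rheumatologist will record two treatment proposals in the clinical history". The step is justified partly as an aid to blinding.

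- The first proposal is "the treatment that he would prescribe if the patient was randomized to the control arm".
- The second is the fallback for a SinnoTest patient without a recommendation, and "the proposed treatment in this case cannot be any of the 3 potentially recommended by SinnoTest".
- When the drug is prescribed 6 to 10 days later, for a control patient or a SinnoTest patient without a recommendation, "the medication previously registered by the usual rheumatologist will be used".
- When SinnoTest does recommend, "the investigator prescribes the treatment defined as the most effective by SinnoTest®, except in case of contraindication" (Innovative procedure).

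On blinding, section 17a states: "Evaluators will also be blinded to the intervention where the subject was allocated". Section 22 says that common adverse events "will be actively inquired by the blind investigator" at each study visit. Section 17b calls the trial single-blind and says that the doctor knows the arm.

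**The concern.** A control patient's drug always equals the recorded control proposal. A SinnoTest patient's drug equals it only when the software, or the fallback, happens to name the same one. The clinical history therefore holds a key to the arm for every patient, and the history is the ordinary working record of a clinic. A step meant to help blinding is kept in a place that can weaken it.

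The primary endpoint is a EULAR response at 6 months based on DAS28-ESR. Two of its four components are the swollen and painful joint counts, which depend on the assessor. EULAR response at M3 is also a criterion for discontinuing, and patients who discontinue are not followed further (section 11b). An assessor's knowledge of the arm could therefore affect both the endpoint and who remains to be measured. Moving one patient across the response threshold changes an arm's rate by 1/90 = 1.1 percentage points, against a design difference of 18.2 points.

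**Working it through.** **Arm size.** The article plans 90 per arm for 65% against 83.2% (65% + 18.2 points), two-sided 5%, power 80%. With pooled variance under the null and no continuity correction:

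n = [1.96·√(2·0.741·0.259) + 0.8416·√(0.65·0.35 + 0.832·0.168)]² / 0.182² = 89.8, so 90.

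The figure reproduces, with power 80.1% at 90 per arm. It serves here only as the denominator.

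**What the record reveals.** Let c be the probability that a SinnoTest patient's drug equals the recorded control proposal. With 1:1 allocation and the protocol followed:

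- Drug differs from the control proposal: SinnoTest arm, with certainty. This applies to a share 1 − c of that arm.
- Drug equals the control proposal: P(control | match) = 1/(1 + c).
- Guessing control on a match and SinnoTest on a mismatch is correct in 1 − c/2 of patients.

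**Inputs for c.** None is given for this trial, so these are assumptions:

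- 49% of control proposals are adalimumab, abatacept or rituximab. The Discussion gives up to 49% for RA patients receiving a bDMARD, a different population.
- SinnoTest makes no recommendation in a share r = 10% to 30%.
- When the control proposal is one of the three drugs and SinnoTest recommends, it names the same drug with probability a = 1/3 to 2/3.
- Without a recommendation, the fallback equals the control proposal whenever that proposal lies outside the three. This is the most matching the Reference procedure allows, so it favours the plan.

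Then c = (1 − r)·0.49·a + r·0.51.

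**Comparison without the proposals.** An evaluator who knows only the drug guesses SinnoTest for one of the three drugs and control otherwise. This is correct in 0.5·(1 − r) + 0.5·0.51 of patients.

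| r | a | c | identifiable of 90 | P(control given match) | correct with proposals | correct with drug name alone |
|---|---|---|---|---|---|---|
| 0.10 | 1/3 | 0.147 + 0.051 = 0.198 | 72 | 0.83 | 90% | 70.5% |
| 0.10 | 2/3 | 0.294 + 0.051 = 0.345 | 59 | 0.74 | 83% | 70.5% |
| 0.30 | 1/3 | 0.114 + 0.153 = 0.267 | 66 | 0.79 | 87% | 60.5% |
| 0.30 | 2/3 | 0.229 + 0.153 = 0.382 | 56 | 0.72 | 81% | 60.5% |

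**Wider range.** With a recommendation in 50% to 100% of patients, 33% to 49% of proposals among the three drugs, agreement from 1/3 to 1, and the fallback either never or always equal to an outside proposal, c runs from 0.06 to 0.50 and correct guesses from 75% to 97%. At one extreme (SinnoTest always recommends and always agrees when the proposal is one of its three, at 49%), overall accuracy is 75.5% with or without the proposals. Even there, 46 of 90 SinnoTest patients would be identified with certainty. The drug name alone never does that, because control patients may receive the same three drugs.

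**The case against.** The strongest reply is that the decisive link is not in the article. Unblinding needs an evaluator who sees both the proposals and the drug. No section says that evaluators read the history, or who counts joints. The full protocol and the manuals mentioned in section 18a are not shown and may restrict access. Proposals in the chart and blinded evaluators are compatible if evaluators never consult it. This stands. A reader might infer that the recording rule reveals the arm or defeats the evaluator blinding, and the article does not support that.

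Other points also stand:

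- Recording the choice in advance fixes the control drug independently of the arm, and the blinding it is meant to help may be the patient's. The step is sound; the question is where the record is kept.
- The drug name alone already leaks information, so only the increment belongs to the proposals.
- A match leaves a 17% to 28% chance of the SinnoTest arm under the inputs in the table.
- The patient global rating comes from a blinded patient and ESR from the laboratory, so only the joint counts are exposed to the assessor.
- A reader might expect bias in favour of SinnoTest. Nothing in the article establishes a direction.

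The reply does not dispose of the point. The concern is not that access detail is missing from a condensed article. The article itself specifies a general record as the place for this information and, separately, claims that evaluators are blinded.

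**Conclusion.** The point holds as an avoidable risk. Under protocol adherence, a mismatch between the recorded control proposal and the drug given identifies a SinnoTest patient to anyone who sees both, and a match only shifts the odds towards control. Under the assumed inputs, about 56 to 72 of 90 SinnoTest patients would be identifiable, and correct guesses would rise from about 60-70% to about 81-90%. These sizes rest on the assumed agreement and no-recommendation rates and on carrying the 49% over to patients who have failed an anti-TNF. They also take the Reference procedure rule that the fallback lies outside the three drugs, although the Innovative procedure text lists those three among the options when nothing is recommended; those passages should be reconciled. How many evaluators would see the record, and the size and direction of any effect on the response rate, cannot be determined from the article. The sample size is unaffected.

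**What to change.** Record both proposals before randomisation in an access-restricted REDCap form (the system already used for allocation) or a restricted source document, open to the prescriber, data manager and monitor, instead of in the general clinical history. This keeps the benefit of fixing the control choice in advance. State also that the M3 and M6 assessor scores the joints before opening the chart and has no access to the proposals or the SinnoTest platform. Scoring first also limits the clue from the drug name.

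The cost is one extra form and a sentence or two of procedure. Usual rheumatologists who are not research staff (section 15) will need access rights or a restricted paper source, because section 19 limits CRF entry to authorised personnel and requires original documents behind the data. No extra staff are needed, since blinded evaluators are already planned. If the full protocol already restricts access in this way, a clarifying sentence is enough.
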